**Methods and analysis:**

The study population will include all PWH and PWoH born between 1940 and 2008, aged 18 or older and living in Sweden sometime between 1983 and 2024. The study population will be linked to six nationwide demographic and healthcare registers. Follow-up will continue until the first incident of CRC, emigration or death. The outcome of interest is CRC. PWH will be matched to negative controls 1:10. A Cox regression analysis will be completed first, and the results will be used as a baseline comparison to the ensemble ML results. A range of ML methods will be used to develop the ensemble model using stacking.

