#### Swedish National HIV Register (InfCareHIV)

The InfCareHIV Register includes data on more than 99% of those diagnosed with HIV in Sweden.^7^ When people are diagnosed or when they immigrate to Sweden with an HIV diagnosis, they are informed that their data will be included in the register but that they may opt-out, and that they may opt-out at any time in the future if they are included. InfCareHIV has collected data from all HIV clinics across Sweden since 2003, and earlier data has been retrospectively added.^7^ The register includes demographic variables, such as legal sex and country of birth, as well as variables relating to HIV acquisition such as date of first positive HIV test and the most likely mode of HIV acquisition. At every follow-up visit, routine measures, such as HIV-RNA levels, CD4(+) T cell counts and current ART, are included in the register.

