#### Total Population Register

The Total Population Register, managed by Statistics Sweden, includes every birth, death, emigration from Sweden, immigration to Sweden, migration within Sweden, marriage and divorce, country of birth, legal sex and citizenship.^25^ The primary purpose of this register is to cover the composition and structure of the Swedish population.^25^

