### Study population

The study population will include all resident PWH and PWoH, 18 years or older, born between 1940 and 2008, who resided in Sweden at any time point between 1983 and 2024. The study period will span from 1 January 1983 to 31 December 2024. The inclusion date will be the day the person turns 18, the start date of residency in Sweden, or the study start date, whichever occurs last. Follow-up will continue until emigration, death, end of study time or until 6 months before the first incident of CRC. The outcome of interest is CRC. See figure 1 for an illustration of the inclusion criteria and how inclusion and the follow-up period were defined.

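### Entry and exit dates take no account of HIV diagnosis or of repeated residency spells, so a returnee can be counted as PWH on time that is wholly before HIV

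*Protocol article*

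**What the plan says.** The protocol article, under Study population, admits anyone eligible by age and birth year "who resided in Sweden at any time point between 1983 and 2024". People who left and came back therefore qualify. Entry is a single date, the latest of the three listed here: "The inclusion date will be the day the person turns 18, the start date of residency in Sweden, or the study start date, whichever occurs". Exit is defined as follows: "Follow-up will continue until emigration, death, end of study time or until 6 months before the first incident of CRC". The abstract also lists emigration as an end point: "Follow-up will continue until the first incident of CRC, emigration or death".

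Three things are absent from these rules: the date of HIV diagnosis, a statement of which residency start or emigration counts when there is more than one, and any mention of what happens on return.

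The data needed are among the sources listed. The Total Population Register "includes every birth, death, emigration from Sweden, immigration to Sweden, migration within Sweden". InfCareHIV holds "variables relating to HIV acquisition such as date of first positive HIV test". The protocol also recognises that some people reach the HIV register by moving to Sweden already diagnosed: "When people are diagnosed or when they immigrate to Sweden with an HIV diagnosis, they are informed that their data will be included".

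**The concern.** A rule with one entry and one exit works if everyone has one residency spell. For a person with two spells the result depends on which dates are used, and the text does not settle this. One natural reading takes the earliest residency start and the emigration that follows it. Under that reading someone first registered with HIV after returning is placed in the PWH group because of something that happened after their follow-up ended.

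At stake is which person-time is called HIV-positive. The section on clinical relevance intends the model for routine visits at Swedish HIV clinics. Time before HIV, attached to a PWH label, says nothing about those visits, and the time that would be informative is the part dropped. The PWH-only substudy rests on the PWH events alone, so misassigned time matters most there.

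**Working it through.** **1. The rule applied to one illustrative person.** The dates are invented. The person was resident in Sweden and over 18 on 1 January 1983, emigrated in 1995, returned in 2010 with HIV diagnosed abroad, and had CRC in 2020.

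| Reading | Follow-up | HIV-care time kept? | CRC kept? |
|---|---|---|---|
| Earliest residency start, first emigration after it | 1983–1995, about 12 years, all pre-HIV | No | No |
| Latest residency start, next emigration after it | 2010 to six months before the CRC, about 9.5 years | Yes | Yes |

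Both readings fit the words. A third pairing, latest start with earliest emigration, would put exit (1995) before entry (2010); nothing in the text calls for it.

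**2. What the label does under the earliest-start reading.** The article does not say whether HIV status is fixed or time-updated.
- Fixed label: 12 pre-HIV years count as PWH time, which is misclassification.
- Time-updated status: the person contributes 12 HIV-negative years and no HIV-positive time.

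**3. Why the latest-start reading is not a full repair.** Suppose the same person returned in 2010 without HIV and was diagnosed in 2014. Entry is still 2010, so with a fixed label 2014 − 2010 = 4 pre-HIV years count as PWH time. The cause is the missing HIV date in the entry rule, not censoring at emigration.

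**4. Size in events.** Inputs from the data preparation section: 13 000 PWH, 130 000 PWoH, median follow-up of at least 10 years, rate 129.1 per 100 000 (taken as per person-year).
- PWH events at the general rate: 13 000 × 10 × 129.1/100 000 = 167.8.
- The share of returnees is not given. Assume 2–10% of PWH, with 50–100% of their time after return.
- Low end: 0.02 × 0.50 × 167.8 = 1.7 events. High end: 0.10 × 1.00 × 167.8 = 16.8 events.
- The high end is a ceiling that cannot be reached, since some follow-up must precede the emigration. If the 10 years already allow for censoring, the calculation also double-counts.

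**5. Size in power.** The plan states 80% power for an HR of about 1.20 at two-sided 0.05.
- Events at exactly 10 years: 130 000 × 10 × 0.001291 + 13 000 × 10 × 0.001291 × 1.20 = 1678.3 + 201.4 ≈ 1 880.
- Schoenfeld, with PWH share p = 1/11: events needed = (1.960 + 0.842)² / [p(1 − p)(ln 1.20)²] ≈ 2 858. Power with 1 880 events is 62.3%.
- Wald on the log rate ratio: SE = √(1/1678.3 + 1/201.4) = 0.0746, and power = Φ(0.1823/0.0746 − 1.960) = 68.6%.
- The stated 80% is therefore not reproduced at 10 years. About 15 years of mean follow-up gives 79.5% (Schoenfeld), which the wording of at least 10 years does not exclude. This gap has nothing to do with the emigration rule; the figures serve here only as a base.
- Removing 2%, 5% or 10% of PWH events takes the Wald power from 68.6% to 67.8%, 66.6% or 64.5%.

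**The case against.** The strongest reply is that the text never says follow-up ends permanently. It says emigration, not first or final emigration, and the abstract attaches the word first to CRC only. A reader might infer that all time after a return is discarded for good, or that a returnee diagnosed later has no HIV-positive time at all. The documents do not establish either. The first needs the earliest-start reading; the second also needs time-updated HIV status. Neither is fixed, and the latest-start reading keeps the 2020 CRC in the example. This part of the reply stands.

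Censoring at emigration is also a standard register rule. Person-time and events leave together, so hazards are not biased unless leaving or returning is related to CRC risk given the covariates. There is a reason not to allow re-entry: the National Cancer Register covers diagnoses made in Sweden, so a CRC found abroad between spells could be missed. This stands too, and it is why re-entry should not be required.

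A reader might further infer that PWH are hit harder because migration is a route into the HIV register. That does not follow. A first-time immigrant enters at the start of residency and loses nothing; only leaving and returning matters, and nothing shown says this is commoner in PWH.

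Finally, Figure 1 is said to illustrate inclusion and follow-up and is not available, and an article may leave spell handling to a fuller document. That excuses silence on re-entry. It does not dispose of the entry rule, which the article states in full and which contains no HIV date.

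**Conclusion.** The point holds in a limited form. The stated entry rule omits the HIV date, and the entry and exit rules do not identify which residency spell is meant. Followed literally on the first spell, they can label a returnee PWH on wholly pre-HIV time and drop the HIV-care years and any CRC in them. That is an error in assigning person-time, not a demonstrated bias of known direction.

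Its size cannot be derived from the document. The range of about 2–17 PWH events rests only on assumed shares of returnees and of time after return. Over a 2–10% loss of PWH events, power falls by about 1 to 4 percentage points (68.6% to 67.8–64.5%, Wald, 10 years, HR 1.20). The effect on power is probably small. The reason to act is that matching, data splitting and every model use these dates, so the rule should be settled before the cohort is built.

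**What to change.** - **PWH entry.** Define an HIV index date: the diagnosis date or, if diagnosed abroad, the date of immigration or re-immigration. Start follow-up at the latest of the existing entry dates and this index date, using the residency spell that contains it.
- **PWH exit.** Censor at the first emigration after that date; leave the other end points as they are.
- **Matched PWoH.** Assign the matched person's index date, require residency in Sweden and no earlier CRC on that date, and apply the same censoring rule.
- **Later spells.** Re-entry is optional, for example as delayed-entry intervals in a sensitivity analysis of the Cox model.

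The cost is some date programming with registers already listed, and the loss of person-time before the index date. No new data are needed.

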**Figure 1 F1:**
[figure not shown]
Diagram illustrating study inclusion process.

### Data analysis plan

A detailed description of the variables of interest under study from each register is provided in online supplemental table 1. Aspects of the study will mirror the protocol applied by Fernández Carbonell and colleagues, and the code available online will be applied throughout.^16^ All data preparation and analysis will be carried out in Stata and Python using Jupyter Notebook in Visual Studio Code.

#### Data preparation

For this study, we will use complete cases only since missing data are minimal. Variables missing more than 10% of the data will be omitted, and after that, any observations with missing data will be dropped.^32^ For the ML analyses, the data will be split 80% into training and 20% into test sets based on follow-up time. The variables in each set will be further prepared to optimise their analysis. Categorical variables will be transformed using one-hot encoding. Normalisation and standardisation of variables will be applied where necessary.

The participants will be matched 1:10 using the entire HIV-negative population in Sweden that fit the criteria. They will be matched on age, legal sex, region of birth and comorbidities including hypertension, chronic obstructive pulmonary disease, diabetes and previous cancer diagnosis.^33
34^ The standardised mean difference of the cohorts will be compared from before and after matching to confirm consistency. Power was calculated using the full anticipated study population consisting of just over 13 000 PWH matched 1:10 to approximately 130 000 PWoH. Median follow-up time is estimated to be at least 10 years in both groups. The expected incidence rate of CRC used for the calculation was the Swedish age-standardised incidence rate reported by the European Commission (129.1 per 100 000 population).^35^ Based on these assumptions and using a two-sided alpha of 0.05, the study is estimated to have 80% power to detect an HR of approximately 1.20 or greater.

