This study will use comprehensive nationwide data and apply machine learning (ML) methods to develop a CRC risk prediction model. PWoH will be included to increase statistical power. Matching will be used to control for key confounders, and appropriate methods will be applied to minimise bias and prevent overfitting during model development. Sensitivity and subgroup analyses will be conducted to compare model performance across different scenarios. ML-based prediction models may be superior to logistic or Cox proportional hazards (PH) regression-based models. Previous research studies have compared these approaches, resulting in varying conclusions. Some ML methods have been observed to perform as good as, or may be favourable to, Cox PH or logistic regression for some prediction tasks.^8–12^ Logistic or Cox PH regression methods may perform prediction tasks better or worse than some ML approaches,^11^ but data-driven approaches using ML have been favoured in some studies due to their ability to understand complex relationships in data, which may have an advantageous prediction performance.^12^ It may be more difficult to motivate an ML approach in a resource- or time-limited setting, in particular if data quality or dimensionality is lower and Cox PH or logistic regression methods can complete prediction tasks to a comparable level.

This protocol will use an ensemble method called stacking,^13^ which will combine the predictions of multiple ML models to produce an overall predicted risk score of CRC. Each ML method relies on different statistical assumptions and processes that may reflect different patterns in the data and offer unique insights into the relationships between variables and the outcome.^14^ By leveraging the estimates from each model in the ensemble, the perspectives from diverse model approaches can be integrated to create a more robust and accurate prediction.^15–17^ The performance of the ensemble model approach will be compared with the performance of a Cox PH regression model.

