#### Cox PH regression

A Cox PH regression model will be used as a baseline performance comparison for the ML methods. This model will favour the simplest approach, and the use of prior knowledge supported by literature will select the most relevant variables. The model performance will then be considered to develop the model for the prediction of cancer among PWH.

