#### ML ensemble model—unsupervised ML

Time Series Split cross-validation (CV) will be used during model training and meta-learning stages. K-means and hierarchical clustering methods will be used for the clustering analyses. The clustering analyses will be performed within each CV fold. The optimal number of clusters for the clustering analyses will be determined using both the Calinski-Harabasz Index and Silhouette Scores.^16
36^ The final number of clusters will be selected based on the estimates from these two methods and applied.

The clustering analyses will be used to observe any differences in the clustering patterns across the outcomes.^16
37
38^ These methods can uncover patterns from the data structure without prior information or further input to the analysis.^39^ By interpreting the most decisive variables during the clustering process additionally using decision trees, their importance in predicting the outcome can be evaluated in the process. K-means clustering will be used to group unlabelled data into the pre-estimated number of distinctive clusters depending on their distances from each other.^38^ The algorithm iteratively runs until there are no significant changes to the clusters. Hierarchical clustering groups two observations together which are most similar, and is iteratively updated until the pre-estimated number of distinctive clusters is reached.^37^ Decision trees will be used to aid interpretation of the clustering decisions from both analyses to determine the important contributing variables to the outcome.^16^ If a difference in the clustering patterns over the outcome is observed, we can interpret the most determining variables in the clustering patterns as potentially important to predicting the risk of developing cancer. Cluster labels will be generated from the training data only to avoid data leakage and added as variables to both the training and test sets in all models.

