#### Stacking and dissemination

Stacking, an ensemble learning method, will be used to combine predictions from the previously described ML models.^43^ The base learners will generate out-of-fold risk scores using Time Series Split, which will then serve as inputs to a Cox-PH model as the meta-learner. Finally, the trained base learners and meta-learner will then be used to generate final risk score predictions on the test set.

The performance of the stacked models will be primarily evaluated using balanced accuracy,^44^ and additionally assessed with the concordance index,^45^ Brier score,^46^ time-dependent area under the curve and area under the precision-recall curve (AUPRC), before variable importance is assessed.^13
47
48^ All metrics will be thoroughly considered, but the balanced accuracy of each prediction performance will be weighted most due to its handling of class imbalance, considering both sensitivity and specificity.^44^ AUPRC is preferred over area under the receiver operating curve due to its ability to better handle class imbalance, which will be a factor in this study.^49^

The model reporting will adhere to the TRIPOD+AI statement.^50^ The variable importance results will additionally be considered separately. A summary of the analysis plan is illustrated in figure 2.

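### The 80/20 training/test split is based on follow-up time, which is part of the survival outcome, and no evaluation set is fixed for the Cox baseline

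*Protocol article*

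**What the plan says.** All references are to the protocol article.

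- **Data preparation** sets the hold-out rule: "For the ML analyses, the data will be split 80% into training and 20% into test sets based on follow-up time". It does not say which end of the follow-up distribution is held out, or whether balancing on follow-up is meant.
- **Study population** defines when follow-up ends: "Follow-up will continue until emigration, death, end of study time or until 6 months before the first incident of CRC". It also fixes the calendar window: "The study period will span from 1 January 1983 to 31 December 2024".
- **ML ensemble model—unsupervised ML**: "Time Series Split cross-validation (CV) will be used during model training and meta-learning stages". **Stacking and dissemination** adds: "The base learners will generate out-of-fold risk scores using Time Series Split". Neither names the variable that orders the rows.
- **Stacking and dissemination** says the trained learners are "used to generate final risk score predictions on the test set". The metrics are balanced accuracy (primary), concordance index, Brier score, time-dependent AUC and AUPRC.
- **Cox PH regression**: "A Cox PH regression model will be used as a baseline performance comparison for the ML methods". That section mentions no split, test set or validation. The Introduction plans the contrast: "The performance of the ensemble model approach will be compared with the performance of a Cox PH regression model". The Abstract says that whichever method performs better will be implemented.

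**The concern.** A test set estimates performance in new people only if membership does not depend on what is being predicted. Follow-up length is the observed time to CRC or censoring. It is fixed only once the outcome is known, and it is not available when a clinician would use the score. Cutting people at a quantile of it gives training and test sets with non-overlapping survival times. Training then learns the wrong absolute risk, and the test set cannot reveal the error.

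The comparison with Cox is also left open. The ensemble is scored on the held-out set, but the split is stated for the ML analyses only and the Cox evaluation data are not given. If the two models are scored on different people, a difference in performance can arise from case mix alone, and this comparison picks the method that goes forward.

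**Working it through.** The protocol gives no figure for the effect of the split, so there is none to reproduce. The check asks what the rule does if applied as written.

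**Inputs from Data preparation:** about 13 000 people with HIV plus 130 000 without, so n = 143 000; CRC incidence 129.1 per 100 000, taken as λ = 0.001291 per year; median follow-up at least 10 years. **From Study population:** at most 42 years of follow-up (1983–2024).

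**Step 1. Closed form.** Assumptions: constant hazard λ, and censoring uniform on 0–20 years (median 10). Events are rare, so follow-up is nearly uniform on 0–20, with its 80% quantile near 16 years and its 20% quantile near 4.

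- True 10-year risk: 1 − exp(−10 × 0.001291) = 1.28%.
- *Longest fifth held out.* Training keeps follow-up below 16 years. At time t its events are unchanged, but its risk set shrinks from (20 − t)/20 to (16 − t)/20. The apparent hazard is therefore λ(20 − t)/(16 − t). Integrated from 0 to 10 this is λ[10 + 4 ln(16/6)] = 0.001291 × 13.92 = 0.01797, a risk of 1.78%. The ratio to truth is 1.78/1.28 ≈ 1.4. In the test set everyone survives past 16 years, so the 10-year risk is 0%.
- *Shortest fifth held out.* Training has nobody with follow-up below 4 years, so the apparent hazard is 0 up to year 4 and λ afterwards. The risk is 1 − exp(−6 × 0.001291) = 0.77%, a ratio of about 0.6. In the test set all follow-up ends by year 4, so nobody is at risk at 10 years.

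Simulations with n = 143 000, under exponential censoring (median 10, cap 42) or uniform 0–20 censoring, agree for the first case: 1.26–1.29% overall, 1.74–1.83% in training, 0 in test.

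**Step 2. A second simulation with other assumptions.** Entry uniform over 42 years, age-dependent competing exit, risk depending on age and one further covariate; three runs; median follow-up about 13 years; 2429–2587 events. The score evaluated is the true risk score, so no model error enters.

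| Evaluation set | Follow-up range (years) | Share of all events | Events by year 10 | C of the true score |
|---|---|---|---|---|
| Full cohort | 0–42 | 100% | 1297–1436 | 0.735–0.740 |
| Random 20% | 0–42 | 19–20% | 248–291 | 0.72–0.75 |
| Longest 20% | above about 26.7 | 7–7.5% | 0 | 0.69–0.73 |
| Shortest 20% | below about 4.5 | 27–30% | 659–762, nobody at risk at year 10 | 0.67–0.68 |

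The C-index falls clearly with the shortest fifth. With the longest fifth the range overlaps that of a random test set, so the loss in C there is less certain than the loss of all early events.

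**Step 3. Consequence for the metrics.** At a 10-year horizon (the protocol fixes none, so this is an assumption), the longest-followed test set has no cases, so sensitivity, and with it balanced accuracy and time-dependent AUC, cannot be computed. The shortest-followed test set has nobody known to be event-free at 10 years, so specificity cannot be computed. If any event during follow-up is classified instead, the event proportion becomes 180/28 600 to 188/28 600 = 0.63–0.66% (longest) or 659/28 600 to 762/28 600 = 2.3–2.7% (shortest), against 2429/143 000 to 2587/143 000 = 1.7–1.8% overall. The chance level of AUPRC moves with that proportion.

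**Step 4. The Cox contrast.** Setting the sections side by side, the ensemble's evaluation set is given and the Cox model's is not. In Step 2 the same perfect score gives about 0.74 in the full cohort and 0.67–0.73 in a follow-up-selected test set. If Cox were scored on the former and the ensemble on the latter, they would differ by up to about 0.07 with no difference between the models.

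**The case against.** *The wording may be shorthand.* It could mean a random split balanced on follow-up, or a calendar split. The text excludes neither, and Time Series Split does not contradict a balanced hold-out, because the hold-out and the cross-validation within training are separate steps. This stands as a reason to call the defect one of the rule as written. It does not save the rule, since neither alternative is stated.

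*Are the cross-validation folds also split on follow-up?* A reader might infer this from Time Series Split read together with the hold-out rule. The documents name no ordering variable, and entry or calendar date is possible. The inference is not supported.

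*Is Cox scored on its own fitting data?* A reader might infer this from the limitation to ML analyses and from the silence of the Cox section. The sentence on cluster labels speaks of training and test sets for all models, though under an ML heading, and the pipeline figure is not shown. In-sample scoring would also matter little in itself: for a simple Cox model with about 2400 events and an assumed 10–20 covariates, simulated optimism was about 0.001–0.003 in C. What stands is that the evaluation set is not fixed. If both models use the same follow-up-selected set, both estimates are distorted, and the direction of the contrast cannot be derived.

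*Time Series Split leaves its first block without out-of-fold scores.* That is true. The share is 19 070/114 400 = 16.7% only if 5 splits are assumed, and the cost shown is lost data for the meta-learner, with no demonstrated bias.

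*The sizes rest on invented entry patterns.* This is fair. The protocol enters everyone already adult and resident at study start in 1983, so real entry is not uniform. The zero early events or empty late risk set follow from the cut itself, whatever the entry pattern.

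**Conclusion.** The point holds as a defect in the stated rule. Splitting on follow-up time, as the protocol defines it, selects the test set on a component of the outcome. Followed literally, training and test follow-up do not overlap, and Brier score, time-dependent AUC and C-index partly measure the split. Under the Step 1 assumptions, 10-year risk in training is about 1.4 times or about 0.6 times the truth, depending on which end is held out; the protocol does not say which.

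The evaluation set for the Cox baseline is a gap that must be closed, because the method choice depends on it. Bias in the ensemble-versus-Cox contrast is certain only if the two are scored on different people, and the documents do not establish that they are.

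The qualitative conclusion rests only on the definition of follow-up and the hold-out sentence. The numerical sizes are illustrative.

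**What to change.** 1. Replace the hold-out rule with one person-level random split drawn before any modelling, keeping matched sets together and stratifying by HIV status and CRC event. If temporal validation is intended, split on entry or index date instead and censor training follow-up at the cut date. That version has a price: with uniform entry over 42 years and no other exit (an assumption), the newest fifth has at most 8.4 years of follow-up and holds 164/3897 = 4% of events.
2. State that Cox and the ensemble are fitted on the same training set and scored on the same test set.
3. For the stacking step, use stratified K-fold so that every training person gets an out-of-fold score. If Time Series Split is kept, name its ordering variable, make it entry date and never follow-up length, and give the number of splits.

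The cost is protocol wording and a different splitter in the code. No extra data are needed.

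### The planning CRC rate of 129.1 per 100 000 is a general-population age-standardised figure that does not match the age structure of the eligible cohort; it is probably too high per person-year, and the stated detectable HR should be re-derived

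*Protocol article*

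**What the plan says.** All references are to the protocol article.

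- **Data preparation, rate:** "The expected incidence rate of CRC used for the calculation was the Swedish age-standardised incidence rate reported by the European Commission". The value printed there is "129.1 per 100 000 population". No adjustment to the ages of the cohort is described.
- **Data preparation, size:** the calculation assumes "just over 13 000 PWH matched 1:10 to approximately 130 000 PWoH".
- **Data preparation, follow-up:** the article then adds, "Median follow-up time is estimated to be at least 10 years in both groups".
- **Data preparation, result:** "using a two-sided alpha of 0.05", the study is said to have "80% power to detect an HR of approximately 1.20 or greater".
- **Data preparation, matching:** age is one of the matching variables, so the controls share the age structure of the PWH.
- **Study population:** people "18 years or older, born between 1940 and 2008, who resided in Sweden at any time point between 1983 and 2024". Follow-up starts at age 18, at the start of residency or on 1 January 1983, whichever is last.

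The article gives no cohort age distribution, no age-specific CRC rates and no expected number of events.

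**The concern.** An age-standardised rate is a weighted average of age-specific rates, with weights taken from a standard population. It is built for comparing populations. It predicts a cohort's events only if the cohort's person-years are spread over age roughly as the standard is. Here the birth-year limit removes all older person-time from the early study years, and age matching carries the same limit into the control group, which supplies most of the events.

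The HR of 1.20 is the only sample-size justification in the article. The number of events among PWH also limits how complex a model the PWH-only substudy and the held-out 20% test set can support. A rate that is too high per person-year makes both look better founded than they may be.

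This concerns an input. It is separate from whether the printed HR follows from the printed figures.

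**Working it through.** **1. The plan's own figure.** Inputs from Data preparation: 13 000 PWH, 130 000 PWoH (exposed share 1/11), 129.1 per 100 000 read as a rate per person-year, 10 years, two-sided alpha 0.05.

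- Events: 143 000 × 10 × 0.001291 = 1846, of which 13 000 × 10 × 0.001291 = 168 are in PWH before any HIV effect. With HR 1.20 in PWH the total is 1880.
- Events needed for 80% power at HR 1.20 (Schoenfeld): (1.96 + 0.84)² / [(1/11)(10/11)(ln 1.20)²] ≈ 2858.
- Power at HR 1.20 with 1846 to 1880 events: 61% to 62%. HR detectable with 80% power: about 1.25.
- Follow-up at which the printed figure holds: 2858 / (143 000 × 0.001291) ≈ 15.5 years on average.

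The stated 80% at HR 1.20 is therefore not reached at 10 years, but is nearly reached (79%) at 15. That is a separate matter. It shows that the result depends on a follow-up time the article gives only as a minimum.

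**2. The age window.** The oldest attainable age is the calendar year minus 1940: 43 in 1983, 53 in 1993, 60 in 2000, 75 in 2015 and 84 in 2024. If every year-by-age cell that the eligibility rules allow is counted equally (an assumption), mean age is 42, with 17% of cells at 60 or older and 3% at 75 or older.

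**3. Illustrative cohort rate.** Assumptions, none of them from the article: incidence rises as age to the power k; the curve is scaled so that a European-type standard population with 19.5% aged 65 or older has a rate of 129.1; all eligible cells have equal weight.

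| k | Cohort rate per 100 000 |
|---|---|
| 3 | 97 |
| 4 | 83 |
| 5 | 72 |
| 6 | 62 |

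This is 62/129.1 = 48% to 97/129.1 = 75% of the planning rate.

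**4. Consequence if the rate is lower.** Log-rank, 1:10. Event counts are before any HIV effect. Power and detectable HR are rounded and change by no more than about 1 percentage point and 0.01 if the extra PWH events are added.

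| Share of 129.1 | Years | Events (in PWH) | Power at HR 1.20 | Detectable HR |
|---|---|---|---|---|
| 100% | 10 | 1846 (168) | 62% | 1.25 |
| 75% | 10 | 1385 (126) | 50% | 1.30 |
| 50% | 10 | 923 (84) | 36% | 1.37 |
| 100% | 15 | 2769 (252) | 79% | 1.20 |
| 75% | 15 | 2077 (189) | 67% | 1.24 |
| 50% | 15 | 1385 (126) | 50% | 1.30 |

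**5. Follow-up can work the other way.** Under the model in step 3, a cohort entering at age 40 and followed for 20 years would have 0.73 (k = 6) to 1.79 (k = 3) times the 1846 events of step 1. A lower rate per person-year therefore does not by itself settle the direction of the error in total events.

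**The case against.** The strongest reply is that events are rate times person-time, and the article fixes only a floor for the second factor. Someone present from 1983 to 2024 could contribute about 42 years, part of it at ages where CRC is common. Even 75% of the rate over 15 years gives 2077 events, more than the 1846 obtained at the full rate over 10. This stands. A reader might infer that the expected events are overstated; the documents do not support that. They state no event count, and the 1846 is a reconstruction at the 10-year minimum.

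The size is also uncertain. Neither the standard population nor the cohort's ages are given. An all-age standard includes children with almost no CRC, whom the eligibility rules exclude, and this pulls the cohort rate up. With other assumed standards, age gradients of power 3 to 5 and bell-shaped cohort ages averaging 40 to 50, the ratio of cohort rate to standardised rate runs from about 0.20 to 1.00. The most favourable case shows no mismatch, though most lie below 0.8. Controls are also matched on diabetes and previous cancer, so they are not an average-risk sample. This too stands, and it rules out quoting any single corrected rate.

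Finally, the study aims are prediction, comparison with a Cox model and variable importance, not estimation of an HIV hazard ratio, and the registers fix the sample. That limits the consequence: no planned analysis changes. It does not rescue the printed power statement, which gives a specific HR from an input not matched to the cohort. Longer follow-up adds person-time but does not make the rate the right one for that person-time.

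**Conclusion.** The point holds as a mismatch between the planning rate and the eligible cohort. The birth-year limit, the study period and the age matching follow directly from the article, and together they make it probable that 129.1 per 100 000 is too high per person-year. A figure of about 62 to 97 per 100 000 is an illustration that depends on the assumed age gradient, the assumed standard and equal weighting of eligible cells. If follow-up were 10 years, 75% and 50% of the stated rate would move the detectable HR from about 1.25 to 1.30 and 1.37, and power at HR 1.20 from about 62% to 50% and 36%.

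The net effect on total events and on the detectable HR is not fixed by the documents, because follow-up is given only as a minimum. The article does not show that the study has too few events. It does show that the stated HR of 1.20 rests on a rate and a follow-up time that have not been made to describe the same person-time.

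**What to change.** Replace the single standardised rate with Swedish age-, sex- and calendar-period-specific CRC rates. Apply them to the actual person-years of eligible PWH by attained age, counted from the inclusion date used in the analysis, with the age-matched PWoH at ten times that. Restate in Data preparation the expected CRC events, overall and in PWH, and the HR detectable with 80% power.

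The cost is a short recalculation on linked register data and a revised sentence or two. The stated HR may become less favourable. No extra participants are needed and no planned analysis has to change.
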